## Abstract

**Background:**

Cardiovascular diseases (CVDs) are one of the leading causes of death and disability in the world. Over 80% of CVD deaths take place in low-and middle-income countries. One-third of the population aged above 40 years suffers from Hypertension (HTN) and this is largely unreported as there is no registry for CVDs. No guidelines are available for use in health care facilities, especially private health facilities where practice among GPs varies considerably. We aim to conduct a Cluster Randomized Controlled trial delivering a quality HTN-CVD care package at strengthened private health facilities as compared to current practice at private health facilities.

**Methods/Design:**

A pragmatic cluster randomized trial, with qualitative and economic studies, will be conducted in Sargodha district of Punjab, Pakistan, from January 2012 to December 2016. At least 912 hypertensives will be registered in the two arms, six clusters per arm. The proposed cluster randomized controlled trial will evaluate the effects of delivering quality HTN-CVD care, through enabled private health care facilities, to achieve better case registration, adherence and hypertension control also blood glucose and serum cholesterol control. The trial will be conducted through the doctors and paramedics at private health facilities. Main outcomes are mean difference in Systolic blood pressure among the two arms. Secondary outcomes are mean change in total serum cholesterol levels and mean change in glycaemic control achieved in the adult hypertensive patients. Individual and Cluster level analysis will be done according to intention-to-treat.

**Discussion:**

Due to the high burden of disease where 1 in 3 individuals aged above 45 suffers from hypertension, topped with the fact that there is a dearth of a set of available, standardised guidelines for management, the disease is constantly on a hike in Pakistan. The government has made no effort to issue a set of guidelines adapted specifically for our population and this becomes more of a problem when managing CVD in urban population through private practitioners whose practices vary widely.If our set of context sensitive guidelines show an effectiveness in the proposed intervention districts it will be replicated in other such settings.

**Trial registration:**

Current Controlled Trials ISRCTN34381594

## Background

### Burden of CVD in Pakistan

The WHO report on Global atlas on cardiovascular disease prevention and control states that cardiovascular diseases (CVDs) are the leading causes of death and disability in the world. Over 80% of CVD deaths take place in low-and middle-income countries [1]. Despite convincing evidence that lowering of blood pressure decreases cardiovascular morbidity and mortality, the control of hypertension has been poor in developing countries due to a multitude of reasons.

According to National Health Survey Pakistan (NHSP) hypertension was shown to affect 18% of adults aged >15 years and around 33% of adults above 45 years [2]. In Pakistan there is a lack of adequate data on the CVD disease burden as well as the risk factors involved.

### Urban health and facilities available

A study done in urban settings (by Jafari et al.) found that 27.6%and 39.3% of hypertensive patients suffer from concomitant diabetes and hypercholesterolemia respectively, whereas 45.3% are smokers [3].

In urban areas, the availability and quality of the first level care public facilities is not adequate. This makes private clinics/ small hospitals an alternate “choice” for the first level care in urban areas. However, in the absence of a regulatory and/or partnership mechanism, the care delivery practices vary widely.

### Public–private mix models in Pakistan

In Pakistan two main models of public-private mix (PPM) emerged so far are the “social franchise” and the “district-led partnership” models. The variants of social franchise model (e.g. greenstar, MSS model) have been tested and found workable for delivering reproductive health and communicable disease care interventions in selected urban areas.

The district-led partnership model has been developed through an extensive and systematic exercise in Pakistan. The exercise included: a) strategic framework and intervention design; b) guidelines and products for planning, implementing and monitoring partnership interventions; c) piloting and evaluation of guidelines and products; and d) scaling-up of the refined model^a^ for TB, malaria, and more recently MDR-TB interventions.

### Involvement of the association

The Association is a not for profit company with vast experience of working in TB, lung health, reproductive health and cardiovascular diseases. The Association and Nuffield Institute have been the lead program technical partners for developing the district-led partnership model in Pakistan. Currently, the Association is responsible for implementing public-private partnership interventions in: 18 districts for DOTS and MDR-TB (TGF R-9), and 2 districts for RBM (TGF Round 7 and 10). This valuable experience and strong field presence will help the Association to implement the proposed CVD-HTN intervention in 1-2 of the districts with an ongoing public-private partnership for communicable disease control.

### Rationale

The proposed implementation research is to develop and evaluate a model of delivering CVD-HTN care package through a network of private clinics, already engaged in communicable disease control activities. The care delivery dimensions that need further attention include: chronicity of disease requiring relatively long-term liaison between patient and care provider, higher prevalence, combination of drugs and lifestyle interventions, and poorly defined management support arrangements at district level.

The CVD-HTN care delivery modalities and products are required for ensuring quality and planning expansion. The proposed exercise is to develop and evaluate an intervention for delivering quality CVD-HTN care through enabled private health facilities. The set of implementation products may include: case management desk guide, training module, recording/reporting and monitoring instruments, and communication tool. These products will cover the technical and operational aspects of managing cases i.e. screening, diagnosis, prescription, education, follow-up etc.

### Aim

The aim is to enhance the delivery of quality CVD-HTN care through private health facilities in urban settings. The conditions to be covered in the care package include: hypertension, type 2 diabetes, and hypercholesteremia.

### Primary objective

To compare the mean change in systolic blood pressure (10 mmHg) in adult patients (>25 years) receiving enhanced CVD-HTN care package with the mean change in systolic blood pressure (5 mmHg) for those receiving routine care at the private facilities in Punjab.

### Secondary objectives

•To compare the mean difference in systolic blood pressure (at least 6 mmHg) due to the intervention.

•To compare the mean change in total serum cholesterol (at least 4 mg/dl decrease) achieved in the adult hypertensive patients.

•To compare the mean change in glycaemic control in the adult type 2 diabetes patients (among registered hypertensive cases) receiving enhanced CVD-HTN care package (2%change in HbA1c) in comparison with the mean change for those receiving routine CVD-HTN care at the private health facilities(1%change in HbA1c).

•To compare the tobacco cessation rate in intervention arm (41%) and control arm (8%).

•Record adverse events of Cardiovascular disease (MI, angina) and cerebro-vascular disease (stroke) among the two arms of the study.

•To conduct incremental cost effectiveness analysis of managing adult hypertensive patients with or without associated conditions (Type 2 diabetes and hypercholesterolemia) at private care facilities in Punjab, Pakistan.

### Research question

•How effective and feasible is to deliver and manage quality care for the control of selected cardiovascular diseases (i.e. hypertension, type-II diabetes, and hyper-cholesteremia) in adults (i.e. > 25 years), through enabled private health facilities as compared to current practice, in urban settings?

The control of selected cardiovascular diseases will be assessed by measuring change in blood pressure, blood glucose, and serum cholesterol.

### Hypothesis

•The enabling of private health facilities for cardiovascular disease intervention for adult hypertensive patients will improve the control of hypertension by decreasing mean systolic BP by at least 6 mm Hg.

•The enabling of private health facilities for cardiovascular disease intervention for adult hypertensive patients will improve the control of Blood glucose (HbA1C < 7.5%) and serum cholesterol (<200 mg/dl) by at least 15% (as compared to the current practice).

## Methods/Design

### Study design

A pragmatic parallel arms cluster randomized controlled trial (c RCT) with two arms will be conducted from January 2012 to December 2016 with a duration of 60 months.

The proposed cluster randomized controlled trial will evaluate the effects of delivering quality HTN-CVD care, through enabled private health care facilities, to achieve better adherence and hypertension control also blood glucose and serum cholesterol control. The trial will have two arms (Figure 1).

**Figure 1 F1:**
[figure not shown]
Flow chart of study.

### Interventions

#### Intervention arm

Quality care will be delivered to adult hypertension patients, through enabled private healthcare facilities. The inputs for delivering quality care at enabled facilities will include: a) context sensitive operational guidelines^b^, b) supplement equipment and communication, c) training and supervisory support, d) patient education materials. The care delivery dimensions to be addressed will include: a) enhanced screening and diagnosis, b) standardized prescription, c) interactive education of patient and family, d) follow-up and adherence, e) recording, reporting and monitoring, f) referral linkage with respective district hospital, g) district health office engagement and support, and h) technical support for in-country research uptake.

#### Control arm

The control for comparison is the current care practices (for hypertension and associated conditions) at the private health care facilities. The only addition will be a) enhanced screening and diagnosis, b) introduction of HTN-CVD register for collecting core data set on patients attending these control facilities. In ‘current practice’, each practitioner manages HTN-CVD cases, as per his/her self-determined regimen and without reference to any specific guidelines and/or tools.

The health staff at a facility will offer the same care package to all its HTN-CVD cases, regardless of their social strata and other preferences. This will reduce the chances of intra-cluster contamination as well as strengthen and simplify the implementation of prospective evaluation. All trial patients will be asked to arrange their prescribed drugs, so that the trial reflects the real life practice in private health care delivery system.

### Study setting

Sargodha is the tentatively proposed district for implementing the research. About one-third of the district population lives in urban areas (i.e. 1 million out of 3.1 million). About 38% of the urban population is above 25 years of age (i.e. 380,000), and about a quarter of these are expected to be hypertensives (95,000).

In Sargodha, the Association has actively been engaged in supporting the implementation of various disease control interventions through district health systems. These include communicable diseases like TB-DOTS and sexually transmitted infection (STI) control, tobacco cessation, public-private partnership, advocacy-communication and social mobilization for disease control, drug management enhancement etc. This experience-based understanding and trust with the district health office would help partners to implement the proposed public-private partnership innovation.

### Study population

In these two districts, *12* private health facilities will be selected into the trial.

#### Identifying participants

A group of private facilities has already been selected for TB-PPM intervention in the district. These facilities have been selected on basis of objective functioning and willingness criteria. The private facilities for HTN-CVD trial will be identified from the already functioning facilities in the district.

The individuals attending the outpatients will be identified and screened for HTN and subsequently for type 2 diabetes, hypercholesterolemia and smoking, as per agreed care delivery guidelines.

#### Approaching participants

The eligible facilities will be approached through district health office for possible inclusion in the trial. Through respective health facility, communal consent will be arranged from the respective catchment populations. The facilities where both staff and the catchment population consent to participate will be selected in the trial.

#### Inclusion/exclusion criteria

Among these private facilities ,all newly diagnosed hypertensive (systolic blood pressure >140 mm Hg, diastolic blood pressure >90 mm Hg) male and female patients aged 25 years or more from the catchment population of the respective facility will be included, after an informed consent. The patients to be excluded from the trial are: a) pregnant women, b) persons with advanced chronic disease, c) person with conditions that cause secondary hypertension, d) person with known history of hypertension and/or CVD treatment in the past, e) person not likely to stay in the area for the required follow-up period of 15 months.

Patients who are pregnant and have hypertension will be referred to a gynecologist, patients with advanced chronic disease to a general medical practitioner, and those with a known history of hypertension and/or CVD treatment in the past will be referred to a cardiologist. Only patients who are new cases of hypertension are included in the trial. People with known hypertension are excluded from the trial as they would already be on some sort of antihypertensive drug regimen which may mask the effects of our intervention.

#### Recruiting participants

The eligible for inclusion patients will be informed and offered to participate (see inclusion/ exclusion criteria above). The patient is recruited only if he/she consents to participate.

Once recruited, each patient in the:

– control arm will be offered standardized diagnosis and care as per current practice, whereas intervention arm will be offered an enhanced HTN-CVD care including standardized diagnosis, prescription, follow-up, and monitoring.

– intervention arm will also be educated on life style modifications recommended for the individual, whereas control arm patients will receive information brochure.

– both arms will be asked to arrange the prescribed medicine through their own sources. However, access to baseline BP, HbA1c, cholesterol examination will be facilitated, for both arms, through trial resources.

Both arms will be requested to adhere to the treatment protocols.

### Data management procedures

Most of the data will be collected as a part of the care delivery process by doctors and paramedics on the ‘CVD card’. Other data related especially to trial will be recorded on the ‘trial registration form (TRF). Research assistant (RA) will visit the identified Lab on monthly basis and will collect test results. RA will visit each centre on monthly basis and will i) check each TRF for completeness and correctness, and those found with missing data will be acted upon accordingly. ii) correlate the Lab results with entries on TRF iii) check for drugs and supplies and reimburse for gaps. RA will send a copy of TRF and Lab test results to the central office i) at test one i.e. baseline ii) at test two i.e. final outcome, for data entry, cleaning and analysis.

#### Data confidentiality and data entry

Each form will be sent as mentioned above by a registered courier service in a sealed envelope. The forms will be kept under lock and key in the central ASD office with only the PI and project coordinator having access to them. Data entry will be done twice by two independent data entry operators to minimize typing errors. Data will be entered on SPSS 20.

### Statistical considerations

#### Sample size

A total of twelve clusters^c^ (i.e. six clusters in each trial arm) will be included in the study, with a minimum of 76 patients recruitment in each cluster and a total of 912 patients in the trial. The assumptions are: a) an intra-class correlation coefficient (ICC) of 0.02, b) design effect of 2.5 [4], c) and standard deviation of blood pressure as 11 mm [5] d) lost to follow-up of 25%. This sample size will give 94% power using 5% level of significance for detecting an assumed difference in the mean change of systolic blood pressure of 6 mm Hg between the intervention and the control arm [6,7].

For a sub group analysis of hypertensive patients with concomitant type-II diabetes, the main assumption is that 27.6% of the recruited hypertensive will have type-II diabetes i.e. 21 patients out of 76 hypertensive recruited at each clinic will be have diabetes [3]. The proposed sample size will give 86% power using 5% level of significance for detecting an assumed difference in mean change of HbA1c of 1% [8,9] between the intervention and the control arms. The assumed standard deviation of HbA1c is 2% [10], and intra-cluster correlation is 0.02 [6,7].

For a sub group analysis of hypertensive patients with concomitant hyper-cholesteremia, the main assumption is that 39.3% of the recruited hypertensive will have hyper-cholesteremia i.e. 30 patients out of 76 hypertensive recruited at each clinic will be have hyper-cholesteremia [3]. The proposed sample size will give 100% power using 5% level of significance for detecting an assumed difference of 4.9 mg/dl [11] between the group means. The assumed standard deviation is 2.9 mg/dl [11], and intra-cluster correlation is 0.02 [6,7].

For a sub group analysis those hypertensive patients who smoke, the main assumption is that 34.5% of the recruited hypertensive will be tobacco smokers i.e. 27 out of 76 hypertensive recruited at each clinic will be smokers [3]. The proposed sample size will give 100% power using 5% significance level for detecting a difference between the group proportions of 0.33 when the intra-cluster correlation is 0.02 [6,7].

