### Phases of the trial

The trial will have the following three phases: Refer to Figure 2.

1) Inception & piloting phase. The main purpose of the two-year phase is to develop, pilot and refine the care delivery guidelines/ materials and trial design/ protocols before embarking upon the trial registration.

– The piloting experiences and results will enable the research team to:

– Assess the feasibility and acceptability, and then accordingly modifythe process for health facility selection (i.e. facility assessment, providers’ and communal consent for the trial etc.) and management support (logistic supplement, reporting, monitoring etc.)

– Assess the feasibility and acceptability, and then accordingly modifythe case management guidelines i.e. diagnosis, treatment, record keeping, follow-up etc.

– Assess the feasibility and robustness of the research protocols, then accordingly modify, the protocols for case inclusion/ exclusion, recruitment rate, and periodic assessment (research related).

– Revisit the assumed proportion of diabetics, dyslipidemic and smoker patients among adult hypertensive patients in local context.

– Revisit the assumptions about sample size calculation to meet the power of the study such as mean change (± standard deviation) in systolic blood pressure, glycaemic and cholesterol control, and tobacco cessation between intervention and control arms.

– Assess and modify, if needed, the proposed statistical methods to analyze the trial data.

– The qualitative interviews with providers (± patients) for assessing the feasibility during the trial piloting will also be adapted subsequently for the trial assessment. In short the trial piloting will inform the decision to implement the trial to get optimal results and valid evidence.

2) Trial Implementation phase

– In the first 03 months of the trial implementation phase, the following arrangements will be made before start registering cases in the trial.

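### The stated 94% power for systolic blood pressure does not follow from the printed inputs, which give about 98% to over 99%; the HbA1c figure of 86% depends on an unstated method

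*Protocol article*

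**What the plan says.** The Sample size section of the protocol article sets the design out in full. There are twelve facilities, six to each arm, and recruitment is described as "with a minimum of 76 patients recruitment in each cluster and a total of 912 patients in the trial". The clustering assumption is "an intra-class correlation coefficient (ICC) of 0.02", from which a design effect of 2.5 is given. The SD is put at 11 mm, and attrition is stated as "lost to follow-up of 25"%. The power claimed for the primary outcome reads: "This sample size will give 94% power using 5% level of significance for detecting an assumed difference in the mean change". The difference in question is 6 mmHg in SBP.

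For the diabetic subgroup it expects 21 of the 76 patients recruited per clinic, with a 1% difference in mean HbA1c change, SD 2% and ICC 0.02. It concludes: "The proposed sample size will give 86% power using 5% level of significance".

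The section names no power formula and no degrees of freedom. It lists the 25% loss with the SBP assumptions only.

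Two other places bear on this. The Primary objective gives expected SBP changes of 10 mmHg and 5 mmHg in the two arms, a difference of 5, while the Secondary objectives, the Hypothesis and the Sample size section use 6. Under Phases of the trial, the pilot is to "Revisit the assumptions about sample size calculation to meet the power of the study".

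**The concern.** The section prints both the inputs and the result for the primary outcome, so the result can be checked, and the two disagree by four to six percentage points. Rounding cannot explain a gap of that size.

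What is at stake is less the size of the trial than whether the calculation can be used. The pilot is to update it, and nobody can update a calculation when one of its inputs is unknown. The printed SD is also described as that of blood pressure, whereas the powered quantity is a mean change, so the reader cannot tell which SD was meant. The HbA1c figure raises a related question: whether it already allows for the 25% loss.

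**Working it through.** **Inputs (all from the Sample size section).** Clusters per arm k = 6. Patients per cluster m = 76, or 76 × 0.75 = 57 after loss. ICC 0.02. SD 11 mmHg. Difference 6 mmHg. Significance level 5%, taken as two-sided because the section does not say; a one-sided test would give still higher power.

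**Formulas.** Design effect DE = 1 + (m − 1) × ICC. Effective patients per arm = k × m / DE. SE = SD × √(2 / effective n). Noncentrality = difference / SE. Power is taken from the normal distribution and from a noncentral t with 2(k − 1) = 10 df.

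**Design effect.** 1 + 75 × 0.02 = 2.5. This reproduces the printed value, so the printed design effect belongs to 76 per cluster, before loss.

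**SBP on the printed inputs**

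| Basis | DE | Effective n per arm | SE | Noncentrality | Normal | t, 10 df |
|---|---|---|---|---|---|---|
| 76 per cluster | 2.50 | 456/2.5 = 182.4 | 1.152 | 5.21 | 99.9% | 99.7% |
| 57 per cluster | 2.12 | 342/2.12 = 161.3 | 1.225 | 4.90 | 99.8% | 99.2% |
| 57 per cluster, DE held at 2.5 | 2.50 | 342/2.5 = 136.8 | 1.330 | 4.51 | 99.5% | 98.2% |

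No row gives 94%. Working backwards with the normal formula, 94% power needs 84 per arm unclustered, 84 × 2.5 = 210 with the design effect, and 210 / 0.75 = 280 after loss. That is 560 patients in all, against the 912 planned.

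**What would give about 94%.** Each line changes one printed input and is a candidate only.

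- SD of change. On 57 per cluster and 10 df, 94% needs a noncentrality of 3.91, so SD = 6 / (3.91 × √(2/161.3)) ≈ 13.8 mmHg. If 11 is the SD of a single reading and the baseline to follow-up correlation is zero (an assumption), the SD of change is 11√2 = 15.6. Power at 57 per cluster is then 93.4% (normal) or 87.6% (10 df).
- ICC. A value of 0.04 gives 94.5% (57 per cluster, 10 df); 0.06 gives 94.0% (76 per cluster, normal).
- Difference. The Primary objective implies 10 − 5 = 5 mmHg. After loss, on 10 df, that gives 95.6%, or 92.2% with DE held at 2.5.

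**HbA1c (difference 1, SD 2, ICC 0.02)**

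| Diabetics per clinic | DE | Effective n per arm | SE | Normal | t, 10 df |
|---|---|---|---|---|---|
| 21 (no loss) | 1.40 | 126/1.40 = 90.0 | 0.298 | 91.8% | 85.5% |
| 15.75 (25% loss) | 1.295 | 94.5/1.295 = 73.0 | 0.331 | 85.6% | 77.7% |

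The printed 86% is therefore reached, within rounding of the inputs, by two standard routes: 10 df without loss, or the normal approximation with loss. Applying either of these routes to SBP still gives over 99%, so the choice of method does not explain the 94%.

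**The case against.** The strongest reply is that the SBP discrepancy is on the safe side. The printed power is lower than its inputs support, 912 patients are more than enough on those inputs, and the pilot is already due to re-estimate the mean change and its SD. All of that stands, and it limits the consequence to the reporting of the calculation. It does not make the 94% correct. Nor is this detail that a journal article may leave to the full protocol, because inputs and result are printed together and disagree.

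A reader might infer that the SD of change must exceed 11, so that 94% is really too high. The document does not support that. Power on 57 per cluster and 10 df stays at or above 94% until the SD of change reaches about 13.8, and at a baseline to follow-up correlation of 0.5 the SD of change is 11 × √(2 × 0.5) = 11 exactly. The zero-correlation reading is not stated anywhere, and the same scaling applied to HbA1c would bring that power down to 49% to 66%, so it does not account for both printed figures.

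A reader might also infer that the 86% for HbA1c is an arithmetic error that falls to 78% once loss is applied. That goes too far as well. Loss alone leaves 86% intact under a normal approximation; 78% needs the loss and 10 df together. The HbA1c comparison is also a subgroup analysis of a secondary outcome, so a power a little below 80% carries limited weight.

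**Conclusion.** The 94% for the primary outcome is wrong as printed. The stated inputs give 98.2% to 99.9% under every two-sided variant tried, so at least one input actually used differs from the text. Which one cannot be settled from the document.

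The error understates power, and on the printed inputs the trial is not too small. The reverse would hold only under an SD of change above about 13.8 mmHg, other inputs as printed (57 per cluster, 10 df).

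The HbA1c figure is dependent on method, not wrong. With twelve clusters and a 25% loss both allowed for, it is about 78%. That rests on a cluster-level comparison with 10 df, which fits the cluster-level analysis named under Planned statistical tests but is not stated as the basis of the power calculation.

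**What to change.** In the Sample size section:

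1. Restate SBP power as about 99% on the printed inputs, or print the SD of change, ICC or difference that produced 94%. Say explicitly whether the SD is that of a single reading or of change.
2. State one common basis for the powers: formula, patients per cluster after 25% loss (57 for SBP, about 16 for HbA1c) and t on 10 df. On that basis HbA1c reads about 78%.
3. Reconcile the 5 mmHg difference implied by the Primary objective with the 6 mmHg in the Sample size section.

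The cost is a rewording of one section and one objective, and a less favourable HbA1c figure. Enrolment does not change. The pilot can then put its own estimates into a calculation that reproduces.

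### The stated 100% power for cholesterol depends wholly on an assumed SD of 2.9 mg/dl that is implausibly small for total cholesterol, and its target and population differ from those in the objective

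*Protocol article*

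**What the plan says.** The Sample size section of the Protocol article plans "six clusters in each trial arm" and expects that "30 patients out of 76 hypertensive recruited at each clinic will be have hyper-cholesteremia". For this subgroup it states: "The proposed sample size will give 100% power using 5% level of significance for detecting an assumed difference of 4.9 mg/dl". It then adds: "The assumed standard deviation is 2.9 mg/dl". The intra-cluster correlation is 0.02. The difference and the SD are cited to the same source. A 25% loss to follow-up is listed for the main calculation and is not repeated for the subgroups.

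The target is worded differently under Secondary objectives: "To compare the mean change in total serum cholesterol (at least 4 mg/dl decrease) achieved in the adult hypertensive patients". The Hypothesis section sets the scale of the outcome by speaking of control of "serum cholesterol (<200 mg/dl) by at least 15" per cent. Planned statistical tests, item c, compares total cholesterol between arms by t-test at baseline, at 15 months and as mean change, and does not restrict this to the subgroup. Under Phases of the trial, the pilot is to revisit the sample-size assumptions, including the mean change and SD for cholesterol control.

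**The concern.** An SD that small implies almost no variation between patients. The limit for control is 200 mg/dl, and 2.9 is about 1.5% of that. The two other continuous outcomes in the same section are planned at about half an SD, while cholesterol is planned at 1.69 SD, and this is the only reason its power comes out at 100%.

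Total cholesterol is a named secondary outcome in the abstract and part of the hypothesis. If the true SD is several times larger, the protocol states a certainty of detection that the design does not have. The calculation and the objective also disagree on the size of the difference and on the patients to be analysed, so it is unclear which comparison the power figure describes.

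**Working it through.** **Inputs from the Sample size section:** 6 clusters per arm; m = 30 per cluster; difference 4.9 mg/dl; SD 2.9 mg/dl; ICC 0.02; 5% significance, taken as two-sided because sidedness is not stated. With 25% loss, m = 22.5.

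**Method.** Design effect = 1 + (m − 1) × ICC. Effective n per arm = 6m / design effect. SE = SD × √(2 / effective n). Power comes from the noncentral t with 2 × 6 − 2 = 10 df (critical value 2.228) and noncentrality difference / SE.

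- No loss: 1 + 29 × 0.02 = 1.58; 180 / 1.58 = 113.9 per arm.
- 25% loss: 1 + 21.5 × 0.02 = 1.43; 135 / 1.43 = 94.4 per arm.

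**Reproducing the plan.** With SD 2.9 and no loss, SE = 2.9 × √(2 / 113.9) = 0.384 and noncentrality = 4.9 / 0.384 = 12.8, so power is 100%. It is also 100% after loss. As a check, the method gives 85.5% for HbA1c (21 per clinic, SD 2, difference 1, no loss), against the stated 86%. A normal approximation with 25% loss also gives 85.5%, so the authors' exact method cannot be settled.

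**What SD 2.9 implies.**
- 1.96 × 2.9 = 5.7 mg/dl on either side of the mean for about 95% of patients.
- Standardised effects: cholesterol 4.9 / 2.9 = 1.69; systolic pressure 6 / 11 = 0.55; HbA1c 1 / 2 = 0.5.

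**Dependence on the SD.** The SDs below are assumptions; the documents give none but 2.9. The difference is 4.9 mg/dl, with 10 df.

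| Assumed SD (mg/dl) | Subgroup, 30 per clinic | Subgroup, 25% loss | All hypertensives, 76 per clinic | All hypertensives, 57 per clinic (25% loss) |
|---|---|---|---|---|
| 10 | 91% | 86% | 99% | 98% |
| 15 | 60% | 53% | 80% | 75% |
| 20 | 39% | 33% | 56% | 51% |
| 30 | 20% | 17% | 29% | 26% |
| 40 | 13% | 12% | 19% | 17% |

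For all hypertensives the design effects are 2.50 and 2.12, and the effective n is 182.4 and 161.3 per arm.

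**SD at which power is 80%.** In the subgroup it is 11.9 mg/dl without loss and 10.8 after loss. In all hypertensives it is 15.0 and 14.2.

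**Normal approximation.** This is more favourable. In the subgroup it gives 69% / 61% (no loss / 25% loss) at SD 15, 46% / 39% at SD 20 and 15% / 13% at SD 40. The 80% points move to about 13.2 and 12.0 mg/dl.

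**Target of 4 mg/dl, as in the objective.** After loss, over SD 20 to 40, power is 24% to 10% in the subgroup and 37% to 13% in all hypertensives.

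**The case against.** The strongest reply is that nothing is miscalculated. The stated inputs do give 100%, and both difference and SD are cited to a source that cannot be seen here. That stands: this is a doubtful assumption, not an arithmetic error.

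A reader might infer that the comparison has a known low power, say 12% to 35%. The documents do not support that. Such a figure needs SDs of about 20 to 40 mg/dl, which appear nowhere in them. At SD 10 the subgroup keeps 86% to 91%, and analysing all hypertensives raises power further. Half an SD, the scale used for HbA1c, would itself imply an SD of 9.8 mg/dl. Nor is it settled which SD is needed: the calculation speaks of group means, the objective of mean change, and the tests cover both. The SD of change need not equal the SD of levels.

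A reader might also infer that 2.9 is a standard error entered by mistake. Without the cited source this cannot be checked, so it forms no part of the point. The comparison of standardised effects is suggestive only, since outcomes need not share one.

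The pilot is already committed to revisiting this SD. That supplies most of the remedy, but it does not correct the figure as stated. Finally, 4.9 mg/dl satisfies a target worded as a minimum of 4, so the difference in target alone is a matter of consistency; the difference in population remains.

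**Conclusion.** The concern holds as a criticism of one input. The 100% rests wholly on an SD of 2.9 mg/dl, which is hard to reconcile with the plan's own scale and stands apart from its other assumptions. Under the t calculation, the subgroup loses 80% power at an SD of about 12 mg/dl, or 11 after loss, which is only 5% to 6% of the 200 mg/dl limit. Beyond that, power depends on an SD the documents do not supply, so only a range can be given.

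These figures rest on a two-sided 5% test, ICC 0.02, equal clinics, 10 df and, where stated, the 25% loss carried over from the main calculation. It is a reasonable worry that a non-significant result would be taken as evidence of no effect because power was stated as 100%, but nothing in the documents says it will be read that way. The mismatch in target and population between Secondary objectives and Sample size needs no assumption. The outcome is secondary, and the power for systolic pressure is untouched.

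**What to change.** 1. Withdraw the 100% figure.
2. State whether the analysed quantity is change or level at 15 months, take its SD from the pilot, and restate power after 25% loss. Until the pilot reports, show power over a range of SDs.
3. Use one target (4 or 4.9 mg/dl) and one population (the subgroup or all hypertensives) in both the objective and the calculation.
4. If the restated power is low, present the cholesterol comparison as an estimate with a confidence interval.

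The cost is wording and a short recalculation, with no extra patients and no new data collection beyond the pilot already planned. The stated power will probably look less favourable.
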